**Ethics and dissemination:**

Ethical approval was obtained from the National Medical Ethics Committee (reference number: 0120-495/2021/6). The results of the proposed study will be disseminated through publication in peer-reviewed journals.

**Clinical Trial Registration:**

[www.ClinicalTrials.gov], identifier [NCT05218798].

## Strengths and limitations of this study

–This study will be the first to investigate the reliability and validity of the 30-15 Intermittent Fitness Test in military personnel.–This study will be the first to compare three different protocols for assessing cardiorespiratory fitness assessment in military personnel.–The study will provide the adopted formula for accurate estimation of maximal oxygen uptake (VO_2_max) for infantry members of the Slovenian Armed Forces (SAF) from the 30-15 Intermittent Fitness test.–The study will provide information about differences in visual attention between better and less physically prepared members of military personnel and its corresponding response following maximal endurance running test. This will enable better understanding of the importance of physical fitness for cognitively demanding situations like those at the battlefield.–A potential limitation of the study is that we will recruit greater number of male than female SAF members, as it is difficult to find an adequate number of female participants who meet the pre-specified inclusion criteria.

## Introduction

Everyday military tasks consist of various movement patterns such as walking, running, jumping, pushing, pulling, lifting, throwing, kicking, dragging, crawling, shooting a firearm, carrying a heavy backpack, and/or other equipment, all of which place a high level of stress on the soldier’s body and mind (Knapik and Whitfield, 2014). Therefore, in order to perform later tasks with ease and greater efficiency, soldiers must possess a high level of physical fitness (Knapik and Whitfield, 2014; Orr et al., 2021). Similar to other physically demanding occupations such as firefighting, and/or law enforcement, muscular strength, strength endurance, and cardiorespiratory fitness (CRF) have been shown to be one of the most important components of a soldier’s physical fitness profile (Herrador Colmenero et al., 2014; Dawes et al., 2021). To test these attributes, there are dozens of individual tests and test batteries, of which the Army Physical Fitness Test (APFT) is the most widely used test battery for military personnel due to its simplicity and ease of administration (Herrador Colmenero et al., 2014; Knapik and Whitfield, 2014). The APFT, which consists of sit-ups, push-ups and a 2-mile run (2_MR_), was introduced in 1980 for members of the U.S. Army. It is design to measure upper body and core muscles strength endurance and CRF (Herrador Colmenero et al., 2014; Knapik and Whitfield, 2014). While muscle strength and core muscle strength endurance are relatively easy to measure, assessing CRF in this special population appears to be more challenging due to the specifics of military operations, which are complex and often unpredictable (Aandstad et al., 2011; Knapik and Whitfield, 2014; Canino et al., 2018). CRF testing is routinely performed by most armed and tactical forces around the world as part of their recruitment process for new members or simply as an annual examination of their personnel (Aandstad et al., 2011; Knapik and Whitfield, 2014). Indeed, direct measurement of CRF during an incremental run on a treadmill (TR) is considered the “gold standard” for estimating maximal oxygen uptake (Vo2max) (Albouaini et al., 2007). However, because of its high cost, complex measurement procedures, and inability to measure more than one person at a time, this method is not routinely used to examine CRF in soldiers (Herrador Colmenero et al., 2014; Knapik and Whitfield, 2014). Therefore, in addition to the 2_MR_, several other field tests such as the 12-mile run, the 3,000-m run, the 2,400-m run, and the 1-mile run are used for CRF evaluation of military personnel (Herrador Colmenero et al., 2014; McGuire and Lockie, 2021). Later tests are usually conducted outdoors. Therefore, weather, climate, and terrain can influence the results and often limit the maximum performance. Although standardized, the most commonly used tests, such as the 2_MR_, have been shown to be difficult for individuals because the pacing strategy is internally controlled (Aandstad et al., 2011). As such, it does not reflect the real situation on the battlefield, where most activities are externally driven by the environment and the enemy. Running patterns on the battlefield are characterized by intermittent, high-intensity shuttle runs with constant changes of direction combined with forward and backward running and turning, while unexpected interruptions of running are common when soldiers are exposed to open fire from the enemy. In those situations, a high level of attention is necessary to support fast and right-decision making to save its’ own live and the lives of other soldiers and civilians. In addition, a high standard of strength and conditioning planning and programming required for military personnel cannot be met with such a test because the final result is expressed as the total time required to run a given distance without any other information needed for training prescription and necessary optimization. Therefore, a new test should be introduced for CRF testing of soldiers that takes into account all of the above, including the specifics of the environment and running patterns similar to those happening on the battlefield (Newell, 1989). Over the past two decades, an intermittent shuttle run testing with 30-15 Intermittent Fitness Test (30-15_IFT_) has been successfully implemented for CRF testing in various populations (Buchheit, 2010; Rabbani and Buchheit, 2015). 30-15_IFT_ is an incremental test consisting of 30-s shuttle runs interspersed with 15-s active recovery periods. At the beginning of the test, a running speed of 8 km/h is set for the first 30-s run and increased by 0.5 km/h in each 30-s phase thereafter. Subjects must run back and forth between two lines 40 m apart at the specified pace determined by a pre-recorded beep. The speed of the last successfully completed stage was recorded as the test result and represents the maximum running speed (MRS) during 30-15_IFT_ (MRS_*IFT*_) (Buchheit, 2008). It has also been shown to reliably predict the VO2max values, suggesting that it can be used for CRF assessment as well as individual training prescription (Buchheit, 2008, 2010). Considering all of the above, we believe that the 30-15_IFT_ may be a suitable tool for measuring CRF of military personnel.

To date, no study has examined the reliability and validity of the 30-15_IFT_ compared to a standard continuous incremental running test and/or a 2_MR_ in infantry members of the Slovenian Armed Forces (SAF). From a practical perspective, it would be of great interest to SAF personnel to provide their strength and conditioning coaches with a valuable measure of CRF to determine and monitor the readiness of SAF infantry members. In addition, we aimed to investigate differences in visual attention between better and less physically prepared infantry members and its corresponding response to maximal endurance running test. Therefore, we hypothesized that the 30-15_IFT_ will prove to be a highly reliable and valid measure of CRF while other parameters such as maximal heart rate (HR_*max*_) and maximal running speed (MRS_*IFT*_) will be valuable indicators of intermittent fitness data for prescribing, monitoring, and optimizing high-intensity interval training in this population. Moreover, it is expected that when compared to less prepared infantry members, a better prepared infantry member will have fewer decline of visual attention following maximal endurance running test.

## Materials and methods

### Study design

The proposed study is a part of a greater project entitled “Enhancement of Physical and Combat Preparedness of Slovenian Armed Force Members; “(original language, Slo: “Dvig telesne in bojne pripravljenosti pripadnikov Slovenske vojske”), which was funded by the Slovenian Research Agency (ARRS) and Slovenian Ministry of Defense (project No. V5-2106; project manager: Assoc. [name]. [name]; principal investigator: Assist. [name]. [name]). This is a randomized cross-over study using a within-subjects test-retest design. To test the current hypothesis, an incremental treadmill test (TR), a 2_MR_ test, and two identical 30-15_IFT_ will be performed in the population of SAF soldiers. For a better understanding of the following text, the term participant is used instead of soldier. The present study will be conducted over a maximum period of 2 weeks per participant. Participants will be instructed to visit the laboratory four times at least 72 h apart. At the first visit, they will be familiarized with the experimental procedures and asked to sign a written informed consent form to participate in the study. Then, participants will be randomly assigned to four experimental conditions (i.e., TR, 2_MR_ and two 30-15_IFT_ running tests).

Additionally, participants will be subsequently divided into two groups based on their score on the APFT (score ranging from 1 to 5). Thus, the higher-scoring group (HSG) is defined as an APFT score of ≥ than 4; and the lower-scoring group (LSG) is defined as an APFT score of ≤ than 2.

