In addition, to determine performance differences between two groups of SAF members, a repeated-measures General Linear Model will be used for main physiological parameters estimated from different tests (TR vs. 2_MR_ vs. 30-15_IFT_) as within-subject factor, whereas groups (HSG vs. LSG) will be used as between-subject factors. Partial eta squared (η^2^) values of 0.01, 0.06, and 0.14 rated difference as small, moderate and high, respectively (Cohen, 1988). Statistical significance for all analysis conducted will be accepted at *p* ≤ 0.05.

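### The HSG/LSG groups rest on an APFT score that includes the 2-mile run and leaves score 3 unassigned: any HSG–LSG test of 2MR time or speed is partly built in, and the group analyses, including visual attention, lose participants

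*Protocol article*

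**What the plan says.** Under Study design the Protocol article states that "participants will be subsequently divided into two groups based on their score on the APFT (score ranging from 1 to 5"). It then fixes two cut-offs. One reads: "the higher-scoring group (HSG) is defined as an APFT score of ≥ than 4". At the other end of the scale the rule is that "the lower-scoring group (LSG) is defined as an APFT score of ≤ than 2". Nothing is said about a score of 3. Under Participants, 32 infantry members are recruited, and no inclusion criterion concerns the APFT score.

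The Introduction describes the test: "The APFT, which consists of sit-ups, push-ups and a 2-mile run".

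The last paragraph of Statistical analysis uses the groups: "to determine performance differences between two groups of SAF members, a repeated-measures General Linear Model will be used for main physiological parameters". The three running tests (TR, 2MR, 30-15IFT) enter "as within-subject factor, whereas groups (HSG vs. LSG) will be used as between-subject factors".

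The groups have a second use. The Abstract links them to differences in visual attention on the d2 test, and the end of the Introduction predicts a smaller post-run decline in the better prepared members.

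**The concern.** There are two separate problems.

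**Overlap of grouping and outcome.** Soldiers are sorted partly by how well they run two miles and may then be compared on how well they run two miles. A difference on that outcome is true by definition of the groups and is not a finding. The study sets the 30-15IFT beside the 2MR. If speed is compared across tests, the 2MR could seem to separate fitter from less fit soldiers better simply because it helped define them.

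**A division that does not cover its scale.** The text speaks of dividing the participants into two groups, but on a 1-to-5 scale the cut-offs cover only 1, 2, 4 and 5. Without recruitment by APFT, the number scoring 3 and the balance of the two groups are left to chance. The visual-attention hypothesis would then be tested on whatever subset remains.

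**Working it through.** **The plan's own figure.** None is given for HSG versus LSG. The only sample-size figure is 6 subjects for the ICC (power 0.90, two-sided 0.05, four observations, ICC 0.80). The usual formula, with an assumed null ICC of 0, gives C = 1/(1 + 4 × 4) = 1/17 and n = 1 + 2(1.960 + 1.282)² × 4 / [(ln C)² × 3] = 4.49, so 5. A null of 0.1 gives 5.61, so 6. The figure is reproduced closely but does not bear on the group comparison.

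**Difference created by the grouping.** Assumptions, since the documents give no values: three equally weighted, normally distributed events with pairwise correlation ρ; study 2MR correlated R with the 2MR inside the APFT; a share p in each tail.

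- Correlation of the study 2MR with the score: r = R × √[(1 + 2ρ)/3].
- For tail cut-off c: mean score in the tail m = φ(c)/p, and variance v = 1 + c·m − m².
- Group difference in within-group SD: d = 2rm / √[1 − r²(1 − v)].

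Low case (ρ = 0, R = 0.8, middle 20% removed, p = 0.4): r = 0.462, c = 0.253, m = 0.966, v = 0.312, so d = 0.892/0.924 = 0.97.

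High case (ρ = 0, R = 1.0, middle 40% removed, p = 0.3): r = 0.577, c = 0.524, m = 1.159, v = 0.264, so d = 1.338/0.869 = 1.54.

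A simulation of 400,000 people gives the same values. With 26 participants (13 vs 13) in the 20% case and 19 (9 vs 10) in the 40% case, a two-sample test at 0.05 would be significant in about 66% to 89% of trials over this range.

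With ρ = 0.3 the simulated range is 1.29 to 2.17 SD, but part of that reflects general fitness. With R = 1.0 and 30% tails, a score without the run has r = 0.6/√2.6 = 0.372 and gives d = 0.863/0.948 = 0.91, against 2.17 with the run included.

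**Loss from the unassigned score.** No APFT distribution is given, so three are assumed. The information in the two-group contrast relative to a slope on the full score is (difference in mean score)² / (1/n₁ + 1/n₂), divided by 32 × Var(score). This takes a linear relation and equal residual variance.

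| Assumed % scoring 1/2/3/4/5 | Unassigned of 32 | HSG, LSG | Mean difference | Contrast | 32 × Var | Ratio |
|---|---|---|---|---|---|---|
| 20/20/20/20/20 | 6.4 | 12.8, 12.8 | 3.00 | 57.6 | 64.0 | 0.90 |
| 10/20/40/20/10 | 12.8 | 9.6, 9.6 | 2.67 | 34.1 | 38.4 | 0.89 |
| 5/10/25/35/25 | 8.0 | 19.2, 4.8 | 2.75 | 29.0 | 39.3 | 0.74 |

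So 6 to 13 participants drop out. The information lost is about 10%, 11% and 26%. In the skewed case (about 19 versus 5), 80% power needs a difference of about 1.47 SD.

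Holding the group difference at 0.8 SD, power falls from 59% (16 vs 16) to 50% and 38% when 20% and 40% are lost. Those figures overstate the harm, because removing the middle also widens the true difference between the groups. The information ratio is the fairer measure.

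**The case against.** The model is declared for physiological parameters. With TR, 2MR and 30-15IFT as levels of one factor it needs an outcome common to all three, such as VO2max, heart rate or lactate. The 2MR finishing time has no counterpart on the treadmill. The 2-mile run section says the time goes into further analysis but does not tie it to this model. This stands in large part. For those outcomes the grouping selects on a correlated trait, which is legitimate. The overlap by construction is confined to time or speed. That reading stays open because the same paragraph speaks of performance differences and because Statistical analysis lists end running speed for all three tests in the correlation analysis.

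The documents also do not say whether the APFT run is an earlier run or the study run; Table 1 does not list the APFT. That is why the size is a range: 1.54 SD is its upper end with uncorrelated events. Some overlap exists either way.

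Comparing extreme groups is a recognised design, and dropping the middle costs only about 10% of the information unless the scores are skewed. This also stands. But such a design recruits on the score or states the exclusion, and here neither is done. Participants scoring 3 do remain in the reliability and correlation analyses and in the overall comparison of the tests.

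A reader might infer that the whole HSG–LSG comparison, visual attention included, is circular. The documents do not support that: d2 is not an APFT event. A reader might also infer that the lower group will be very small or that a group-by-test interaction is certain. No score distribution is given, and no interaction was calculated.

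**Conclusion.** The point holds in limited form. If 2MR time or speed is compared between the APFT-defined groups, about 1.0 to 1.5 SD of difference arises from the grouping alone, even with uncorrelated events. This rests on equal weights, a retest correlation of 0.8 to 1.0 and the middle 20–40% removed. For VO2max, heart rate or lactate the claim does not go beyond selection on a related trait, and it would be wrong to say that those results cannot be read as physiology.

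The score-3 gap is certain from the text; its size is not. The loss affects only the HSG/LSG analyses and is modest unless scores are skewed. The ICC reliability analysis is untouched. The change should be made, because a stated hypothesis and a planned model depend on these groups.

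**What to change.** 1. **Visual attention.** Analyse d2 and its pre-to-post change in all 32 participants, with the full 1-to-5 APFT score as a continuous predictor. Treadmill VO2max is an alternative for d2 only, and it narrows the question to aerobic fitness, whereas the APFT also covers strength endurance. Keep HSG and LSG for description, and state that a score of 3 belongs to neither.
2. **Model across the three tests.** Name the outcomes. Do not test 2MR time or speed between APFT-defined groups, or report it as descriptive and built in by the grouping. Do not use treadmill VO2max as the fitness predictor here: TR is one of the outcomes, so the same overlap would return.

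Regrouping on push-ups and sit-ups alone would also remove the overlap, but it needs event-level APFT results, which the article does not say are held.

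The cost is a change of analysis wording, with no new measurements or participants. The d2 result becomes a slope per APFT point (or per unit of VO2max) instead of a difference between two group means, and it assumes an approximately linear relation.

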### Participants

Thirty-two SAF infantry members (males, *N* = 27) will be recruited for the proposed study. Inclusion criteria are: age 18–40 years, both male and female SAF infantry members who are performing regular military tasks on daily basis, with no history of injuries in the last 6 months prior to recruitment, have not reported any musculoskeletal pain, with no history of chronic musculoskeletal, metabolic, pulmonary, neurological and cardiovascular diseases. Participants will be instructed to avoid any strenuous physical activity for at least 3 days prior to the start of the first testing session and during the course of study, which will be monitored by their superiors. They will be requested to refrain from consuming ergogenic substances and caffeinated beverages prior to the tests. Before the initial assessment on each testing day, a brief meeting will be held to explain the study protocol in detail.

### Experimental protocol

All tests will be performed at the facilities at the Faculty of Sport (University of Ljubljana, Slovenia) between 8 a.m. and 13 p.m. The actual arrival of participants to the testing location will be pre-planned and coordinated with the commanding officers. Each testing group will have 6–8 members in total and they will be instructed to arrive at least 15 min before actual testing, that is 7:45 A.M. The testing procedures will be than explained in detailed and demonstrated by the well experienced faculty staff members. The timeline of testing procedures is explained in detail in Table 1.

**TABLE 1 T1:** Timeline of study protocol.

Activity/Measurements	Time (min)
Body height, weight, and body composition	5
Test of visual attention (d2)	5–10
Supine rest (initial heart rate monitoring)	10–15
Warm-up routine—upright cycling 5 min (1 w pr kg of body weight, 70 rpm) Part I	15–20
Dynamic stretching Part II	20–24
Specific warm-up (running 8 km/h) Part III	24–30
Actual aerobic test (TR, 2_RM_ or 30-15_IFT_)	30–55
Supine rest (post-test heart rate monitoring)	55–60
Test of visual attention (d2)	60–65

TR, treadmill run test; 2_RM_, 2-mile running test; 30-15_IFT_, Intermittent Fitness Test; rpm, revolutions per minute.

### Measurements

#### Anthropometrics

Body mass and height will be measured using a stadiometer and scale anthropometer (GPM, Model 101, Zurich, Switzerland) to the nearest 0.1 cm, while body mass was assessed with multifrequency bioelectrical impedance (InBody 720: Biospace Co., Ltd., Seoul, South Korea) to the nearest of 0.01 kg. Additionally, fat mass, body fat percentage, skeletal muscle mass, fat free mass and total body water were calculated using manufacturer’s algorithm like elsewhere (Seino et al., 2015).

#### Attention assessment

The d2 test was used to determine the level of concentrated visual attention of participants (Bates and Lemay, 2004). It consists of 14 rows with 47 characters per line. These characters are the letters d or p, with a total of one to four dashes located above and/or below each letter. Participants will be instructed to scan each line and cross out only the characters containing the letter d with two dashes during 20 s. After completion of the d_2_ test, two variables will be calculated—concentration performance (CP) and total number of total errors (TE) made by the soldiers. CP is calculated as the number of correctly marked d_2_-symbols minus the number of incorrectly marked symbols (symbols that are not d_2_-symbols). The TE will be assessed as the number of errors made by participants by failing to correctly identify a d_2_-symbol plus the number of errors made by incorrectly marking symbols that were not d_2_- symbols.

#### Maximal aerobic capacity testing equipment

A K5 a portable gas analyzer (COSMED, Italy) will be used to obtain physiological parameters. The device provides reliable values for oxygen uptake volume (VO_2_), carbon dioxide production volume (VCO_2_), and pulmonary ventilation (VE) in a breath-by-breath manner. In addition, capillary blood samples from the earlobe will be collected for all tests (before, immediately after, 3 min after and 5 min after) and the samples will be analyzed for blood lactate concentration [(LA^–^)] using a Biosen C-line analyzer (EKF Diagnostics, Germany).

Simultaneously, a heart rate will be measured by Garmin Edge 830 Pack heart rate monitoring belt (Kansas, United States). The data will be recorded in 5-s interval and automatically analyzed by using the original Polar software.

#### Incremental treadmill test

After 5 min of baseline measurements, while standing on the treadmill (HP Cosmos, Germany), the participants will warm up at 8 km/h run and constant gradient of 1% inclination (Jones and Doust, 1996). Then, they will execute the actual test by running until volitional exhaustion where the running speed will be increased progressively by 2 km/h per minute. The achievement of VO_2max_ was identified as the plateauing of VO_2_ (<2.1 ml/kg/min decrease) despite an increase in workload (Poole and Richardson, 1997). If the above-stated criterion was not fulfilled, the participants will be asked to perform a further constant-speed test equal or higher than the highest speed achieved at the end of the incremental test, as recommended (Rossiter et al., 2006). Throughout the test, respiratory gases will be continuously measured breath-by-breath and reduced to 10-s averages (Borszcz et al., 2018). MRS will be determined as the minimal running velocity that elicited VO_2_max over a period of 30 s.

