#### Statistical analysis

All data will be presented as mean ± SD with 90% confidence interval limits (90% CI). All statistical analysis will be conducted using the SPSS statistical software (version 27.0, IBM Inc., Chicago, United States). Descriptive statistics will be used to summarize demographic characteristics of participants and outcomes. Normality od the data will be confirmed by using the visual inspection of histogram and Q-Q plot and analytically by Shapiro-Wilk test, while the homogeneity of variances of normally distributed variables will be tested by using Levene’s test.

Differences in key physiological outcomes between the different CRF tests (TR vs. 2_MR_ vs. 30-15_IFT_) will be assessed by One-Way ANOVA analysis. The relative reliability of all dependent variables between two 30-15_IFT_ trials will be estimated using the ICC, two-way random effects model (consistency type). ICC values will be classified as very high if > 0.90, high if between 0.70 and 0.89, and moderate if between 0.50 and 0.69. The following criteria will be used to declare good reliability: CV < 5% and ICC > 0.69 (Buchheit et al., 2011). In addition, the standard error of the estimate (SEM) and the coefficient of variation (CV) will be calculated as measures of absolute reliability, indicating the within-subject variation, as previously proposed (Hopkins, 2000). To further address the reliability of the data, bias and random error will be calculated, followed by the minimal detectable change (MDC). To test the usefulness of the IFT, the spreadsheet provided by Hopkins will be used (Hopkins). Usefulness will be determined by comparing the smallest worthwhile change (SWC) with the typical error of measurement (TE) and will be interpreted as follows: “Marginal” (TE > SWC), “OK” (TE = SWC) and “Good” (TE < SWC) (Hopkins, 2007).

Relationship between VO_2max_, HR_peak_ and end running speed of 30-15_IFT_, TR, and 2_MR_ will be assessed using Pearson’s correlation (r). Also, the relationship between VO_2max_ obtained from TR, 2_MR_, and 30-15_IFT_ will be investigated. The following thresholds of the correlation coefficient will be used to assess the magnitude of the relationships analyzed: weak ≤ 0.35; 0.36 ≤ moderate < 0.67; 0.68 ≤ high < 1 (Taylor, 1990).

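### The treadmill plateau criterion bounds a fall in VO2 where it should bound the rise, so as written it is not a usable test for having reached VO2max

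*Protocol article*

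**What the plan says.** All of the rule stands in the Protocol article under Incremental treadmill test. After a warm-up, "the running speed will be increased progressively by 2 km/h per minute" until volitional exhaustion. Gas exchange is "continuously measured breath-by-breath and reduced to 10-s averages". Attainment of VO2max is "identified as the plateauing of VO_2_ (<2.1 ml/kg/min decrease) despite an increase in workload". The next sentence makes this a trigger: "If the above-stated criterion was not fulfilled, the participants will be asked to perform a further constant-speed test equal or higher than the highest speed" reached in the incremental test. The same section ties a second quantity to the result: "MRS will be determined as the minimal running velocity that elicited VO_2_max over a period of 30 s".

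Two other places show what depends on the measurement. The Introduction says that "direct measurement of CRF during an incremental run on a treadmill (TR) is considered the" gold standard for VO2max. Under Statistical analysis, "the relationship between VO_2max_ obtained from TR, 2_MR_, and 30-15_IFT_ will be investigated". No other section restates the plateau rule or corrects its direction.

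**The concern.** The sentence contains two ideas that do not fit together. The first is a plateau while workload goes up; the failure to plateau is then a continued rise, and a numerical tolerance has to cap that rise. The second is the parenthesis, which caps a decrease. Depending on how the parenthesis is read, it either rejects traces that are flat or creeping up by a trivial amount, or it accepts traces that are still climbing steeply.

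The threshold is operative. It decides who is taken to have reached VO2max in the test against which the 30-15 IFT is to be validated, and who is asked to run again. Two operators who follow the text faithfully could classify the same trace differently.

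**Working it through.** The article gives no figure for this rule that could be reproduced, so the check is of the wording, with an illustration of how each reading behaves.

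**Inputs.** The threshold of 2.1 ml/kg/min and the word decrease come from the treadmill section. The SD of the difference between two successive VO2 values is not in the article; it is assumed here to be s = 0.5, 1, 2 or 3 ml/kg/min. The true changes examined, also chosen for illustration, are 0 (flat), +1 (trivial rise) and +4 (still climbing).

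**Set-up.** Let D be the observed change in VO2 from one workload to the next higher one, D ~ N(μ, s²), with Φ the standard normal distribution function.

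- (a) Literal, a fall between 0 and 2.1: P(−2.1 < D < 0) = Φ(−μ/s) − Φ((−2.1 − μ)/s)
- (b) Algebraic, decrease −D below 2.1, so that any rise passes: P(D > −2.1) = 1 − Φ((−2.1 − μ)/s)
- (c) Restated, a rise below 2.1, with falls also passing: P(D < 2.1) = Φ((2.1 − μ)/s)

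**Examples.**

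- Flat VO2, s = 2, reading (a): Φ(0) − Φ(−1.05) = 0.500 − 0.147 = 0.353.
- Rise of 4, s = 3, reading (b): 1 − Φ(−2.03) = 0.979.
- Flat VO2, s = 2, restated (c): Φ(1.05) = 0.853.

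**Probability of meeting the criterion:**

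| True change μ | Reading | s = 0.5 | s = 1 | s = 2 | s = 3 |
|---|---|---|---|---|---|
| 0 | (a) literal | 0.50 | 0.48 | 0.35 | 0.26 |
| 0 | (b) algebraic | 1.00 | 0.98 | 0.85 | 0.76 |
| 0 | (c) restated | 1.00 | 0.98 | 0.85 | 0.76 |
| +1 | (a) literal | 0.02 | 0.16 | 0.25 | 0.22 |
| +1 | (b) algebraic | 1.00 | 1.00 | 0.94 | 0.85 |
| +1 | (c) restated | 0.99 | 0.86 | 0.71 | 0.64 |
| +4 | (a) literal | 0.00 | 0.00 | 0.02 | 0.07 |
| +4 | (b) algebraic | 1.00 | 1.00 | 1.00 | 0.98 |
| +4 | (c) restated | 0.00 | 0.03 | 0.17 | 0.26 |

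**What the table shows.** Reading (a) screens out continuing rises, but it also rejects at least half of truly flat traces. That ceiling of 0.50 needs only symmetric error, because half of the observed changes around a flat VO2 are rises; it does not depend on s. Reading (b) works backwards: the steeper the rise, the more surely it passes. Only (c) accepts most flat traces and rejects most continuing rises, although it too weakens as s grows.

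**The case against.** The strongest reply is that this is a slip of one word. The governing idea in the sentence is a plateau under rising workload, the parenthesis only supplies a tolerance, and experienced staff would not reject an unchanged VO2. That is plausible and limits the severity. It does not make the criterion right: the number is the only objective part of the rule, and it is attached to the wrong direction.

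Three stronger conclusions are tempting, and the article does not support them.

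- *True plateaus will fail, and many participants will run a needless second bout.* This follows only from the literal reading; the algebraic one errs the other way. Nor can the share be fixed. With an assumed mean change of +0.5 ml/kg/min, the gap between the restated and the literal rule runs from 0.46 (0.703 − 0.241, s = 3) to 0.84 (0.999 − 0.159, s = 0.5), and it arises only if staff apply the literal reading.
- *Treadmill VO2max, and with it the validity correlation, is biased.* Failing the criterion excludes nobody. It leads to another run at or above the top speed, which can confirm or raise the observed peak. Under the algebraic reading some submaximal peaks might go unverified, but nothing in the article allows the size of that to be calculated.
- *The extra run contaminates post-test lactate, heart rate and d2, which are then compared between tests.* The article does not say when the further run takes place. Table 1 shows one slot for the aerobic test (30–55 min), then supine rest (55–60) and d2 (60–65), and does not place the further run. The planned between-test comparisons concern physiological outcomes; visual attention is posed as a contrast between better and less prepared members.

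**Conclusion.** The criterion is wrong as written; the severity is minor. The direction of the threshold conflicts with the plateau that it is meant to define, no other section corrects it, and neither available reading gives a rule that can be relied on to tell a plateau from a continuing rise. The finding about wording needs no assumption. The ceiling of 50% for a flat VO2 under the literal reading needs only symmetric error. All other probabilities rest on the assumed normal changes and on SDs of 0.5 to 3 ml/kg/min. No bias in treadmill VO2max is demonstrated, and any effect on post-test measures depends on the unstated timing of the further run.

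**What to change.** Under Incremental treadmill test, restate the criterion as an increase in VO2 of less than 2.1 ml/kg/min despite the increase in workload. With that wording, a flat VO2 passes with probability 0.76 to 1.00 and a continuing rise of 4 ml/kg/min with probability 0.00 to 0.26 over the same assumed SDs. Record in the dataset, as a yes/no variable, which participants performed the further constant-speed run, so that its influence can be examined whenever it took place. The cost is one word in the text and one variable in the data; sample size, visits and analyses are unchanged.
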